#### 662 Health economic data collection

663

664 In order to collect data on the cost of the interventions, health service use and wider  
665 costs/benefits to society, we will record study participant primary and secondary care health  
666 and social care service use over the follow-up period using a client service receipt inventory  
667 (CSRI) to collect service use data from participants, and further triangulated with linked  
668 routinely collected data. We will make use of national unit costs and routine hospital  
669 data/manufacturers data to cost the intervention and service use. We will also consider the  
670 financial implications of presenteeism and absenteeism by calculating the number of  
671 participant workdays lost during the follow-up period and triangulating with income data.

672

673 Health economic data analysis

674

675 We will conduct an economic evaluation at the end of the 3-month follow-up period, based  
676 on the following components:

- 677     • Conduct a primary cost-utility analysis using the EQ-5D-5L as the measure of utility  
678     to generate a cost per QALY estimate.
- 679     • Conduct a secondary cost-effectiveness analysis using the relevant trial outcomes  
680     (Bangor Goal Setting interview, HADs), and develop incremental cost-effectiveness  
681     ratios (ICERs) to express cost-effectiveness.
- 682     • For all analyses, we will use bootstrapping to produce cost-effectiveness  
683     acceptability curves for comparison with the NICE ceiling of £20,000 to £30,000 per  
684     QALY in the UK to communicate to policymakers the probability that the  
685     intervention is cost-effective.
- 686     • Conduct sensitivity analyses to investigate uncertainty in the data.

687 The incremental costs and consequences of the treatment arms will be compared and  
688 expressed in cost per QALYs where possible. We will use a UK tariff as a source of EQ-5D-  
689 5L values for the cost-utility analysis and compare values to UK population norms. In the  
690 event that neither intervention is found to have a significant effect on patient outcomes, we  
691 will be unable to perform a robust analysis of cost-effectiveness. We will therefore present a  
692 cost-consequence analysis, whereby the costs and effect data are presented in a  
693 disaggregated manner. Additional cost-effectiveness analyses using the secondary  
694 outcomes will be carried out for comparative purposes

695

696 We will use both deterministic and probabilistic sensitivity analysis to test uncertainty of  
697 findings. Sensitivity analysis is used in economic evaluations to test how sensitive the  
698 findings are to basic assumptions used in the economic evaluation model. For instance, the  
699 cost of an intervention is to some extent based on assumptions about unit costs and staff  
700 time, likewise effects are subject to uncertainty between individuals. By varying  
701 these assumptions the stability of findings can be tested, and uncertainty can be accounted  
702 for.

703 Deterministic sensitivity analysis can be either univariate or multivariate, where-by single or  
704 multiple parameters may be individually adjusted (within a given range of uncertainty) to test  
705 findings of the model. For instance, the cost of the intervention may be incrementally  
706 increased or decreased (within given confidence limits) to examine the impact on cost-  
707 effectiveness or costs per QALY outcomes. Probabilistic sensitivity analysis assigns a  
708 distribution of point estimates to each parameter and randomly selects a single value for  
709 each model calculation. By running a number of replications, for instance 5000, an ICER  
710 plane can be generated to illustrate the potential variation in cost-effectiveness based on  
711 altering basic assumptions about effectiveness and costs.

712

713

714

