184    affected, and will include remediation, compensatory and adaptive strategies. The  
185    programme will be co-produced in collaboration with a group of people living with cognitive  
186    Covid, led by a PPI co-investigator. At the end of Workstream 2 we will produce a freely  
187    available "Covid-19 Cognitive Recovery Guide" for affected people, their close contacts and  
188    clinicians.

189    A randomised controlled trial will compare the intervention (cognitive rehabilitation) against  
190    standard of care (management of fatigue, anxiety and sleep), with the primary outcome  
191    being participant-set goals (measured using the Bangor Goal Setting Interview) at three  
192    months. Secondary outcome measures will be measures of cognition and quality of life at six  
193    months. With a very conservative effect size of 0.7 and estimated attrition rate of 25%, a  
194    sample size of 118 (50:50 randomisation) is required.

195    The health economic benefits of treatment will be assessed in terms of health resource  
196    utilisation, primary (cost per QALY) and secondary cost-utility analyses and generation of  
197    cost-effectiveness acceptability curves.

198

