#### 5.2.2.1 Trial design

This will be an individually randomised parallel group controlled trial, comparing the study intervention (cognitive rehabilitation) with the clinical standard of care (current clinical management pathways for long Covid, including treatment for fatigue, respiratory disorders, sleep, anxiety and depression).

590

591 5.2.2.2 Participant flow

592

593 Post-consent participants will undergo baseline assessment before randomisation to receive  
594 either neuropsychological rehabilitation or treatment as usual.

595

596 5.2.2.3 Outcome measures

597

598 The primary outcome will be participant-reported goal attainment at 3 months post-  
599 randomisation. This will also be collected at the 6 month post-randomisation follow up. This  
600 will be collected using the Bangor Goal Setting Interview (BGSi).

601

602 Secondary outcomes will be:

- 603 • Cognitive function (tested using the cognitive batteries employed for Workstream 1)
- 604 • Quality of life (EQ-5D-5L)
- 605 • Life Space Assessment
- 606 • Social Functioning (SF-DEM)
- 607 • Instrumental Activities of Daily Living (IADL) Scale
- 608 • Generalised Anxiety Disorder Assessment (GAD-7)
- 609 • Patient Health Questionnaire (PHQ-8)
- 610 • Chalder Fatigue Scale
- 611 • Pittsburgh Sleep Quality (PSQI)
- 612 • DePaul Symptom Questionnaire – Post-Exertional Malaise (DSQ-PEM).
- 613 • Client Service Receipt Inventory (CSRI)

614

615 5.2.2.4 Health economic analyses

616

617 From a public sector, multi-agency perspective we will conduct an economic evaluation to  
618 determine the incremental cost-effectiveness of the intervention in comparison to clinical  
619 standard of care. The intervention of interest will be a novel neuropsychological rehabilitation  
620 intervention programme for cognitive Covid compared to clinical standard of care (i.e. current  
621 clinical management pathways for long Covid, including treatment for fatigue, respiratory  
622 disorders, sleep, anxiety and depression). We will examine two research questions during  
623 the economic evaluation:

624

- 625 1. What is the incremental cost-effectiveness of CICERO-Rehab compared to standard  
626 clinical care for cognitive Covid?
- 627 2. What is the cost per QALY of CICERO-Rehab compared to standard clinical care for  
628 cognitive Covid, and does this fall below the NICE threshold of £20,000 to £30,000  
629 per QALY?

630

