#### 643 Health economic outcome measures

644

645 For the primary cost-effectiveness analysis, the primary outcome will be QALYs, derived  
646 from the EQ-5D-5L outcome measure. The EQ-5D-5L is a generic, preference based,  
647 health-related quality of life (HRQoL) measure. It consists of two parts, a five  
648 item questionnaire and a visual analogue scale (EQ-VAS). The EQ-5D-5L questionnaire is  
649 scored between 0 and 1, with 1 meaning full HRQoL and 0 death (some scores may fall  
650 below 0). Each set of answers on the EQ-5D-5L is assigned a utility score between 0 and 1  
651 based on general population weighting of health states. This measure can then be used to  
652 generate QALY estimates by assigning a quality of life weight to the length of time a person  
653 is in a given health state.

654

655 Secondary cost-effectiveness analyses will be conducted using the Bangor Goal Setting  
656 Interview and HADs outcome measures. These will be used to develop incremental cost-  
657 effectiveness ratios (ICERs) to express cost-effectiveness in natural units of effect, which will  
658 in turn allow comparison with the QALY outcomes. Comparing these outcomes will help to  
659 determine relative agreement between the generic QALY outcomes and 23 clinically relevant  
660 outcomes.

661

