### **5.2 TIME POINTS OF OUTCOMES MEASURES**

Outcome measures are collected at baseline, 3 months and 6 months post-randomisation. Appendix 1 contains a list of all data collected during the study.

The primary outcome is participant-reported goal attainment at 3 months post-randomisation. This will also be collected as a secondary outcome at the 6 month post-randomisation follow up. This will be collected using the Bangor Goal Setting Interview (BGSi).

Secondary outcomes will be:

- Goal Satisfaction Scale ((using the Bangor Goal Setting Interview Scale)
- Cognitive function (tested using the cognitive batteries employed for Workstream 1)
- Quality of life (EQ-5D-5L)\*
- Life Space Assessment
- Social Functioning (SF-DEM)
- Instrumental Activities of Daily Living (IADL) Scale
- Generalised Anxiety Disorder Assessment (GAD-7)
- Patient Health Questionnaire (PHQ-8)
- Chalder Fatigue Scale
- Pittsburgh Sleep Quality (PSQI)
- DePaul Symptom Questionnaire – Post-Exertional Malaise (DSQ-PEM).
- Client Service Receipt Inventory (CSRI)\*

Cognitive function will be assessed using three complementary assessments (expanded below), to maximise understanding of cognition

- Cognitive function assessment 1 – battery of Cognitive tests
  - The Repeatable Battery for the Assessment of Neuropsychological Tests (RBANS)
  - The Delis-Kaplan Executive Function System: The Trail Making Test (Condition 2: Number Sequencing & Condition 4: Number-Letter Switching)
  - The Delis-Kaplan Executive Function System: Colour-Word Interference
  - The Delis-Kaplan Executive Function System: Phonemic Fluency
  - Wechsler Adult Intelligence Scale III: Digit Span
  - Test of Premorbid Functioning (TOPF)
- Cognitive function assessment 2 – online battery of cognitive tests
  - Gorilla
  - 4 Mountains (4MT)
- Cognitive function assessment 3
  - Neotiv suite

\*Health economic data not being analysed at by NWO.

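### The economic evaluation is set at 3 months although EQ-5D-5L and CSRI are scheduled to 6 months, and one secondary ICER uses HADS, which the trial does not collect

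*Combined protocol and SAP*

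**What the plan says.** On the horizon, the health economic data analysis text in Protocol 5.2.2.4 states: "We will conduct an economic evaluation at the end of the 3-month follow-up period". The same section records service use and lost workdays over a follow-up period whose length it does not give, and omits discounting because follow-up is shorter than 12 months, which fits either 3 or 6 months.

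SAP 5.2 states: "Outcome measures are collected at baseline, 3 months and 6 months post-randomisation". Its list of secondary outcomes includes "Quality of life (EQ-5D-5L") and "Client Service Receipt Inventory (CSRI"), both marked as health economic data that the trials unit will not analyse. The Methods part of the protocol's scientific summary reads "Secondary outcome measures will be measures of cognition and quality of life at six" months. The footnote to the SAP's aims places health economics outside the SAP, and SAP Appendix 1 gives no timepoints for EQ-5D-5L or CSRI. The SAP therefore does not settle the horizon.

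On the outcomes, Protocol 5.2.2.4 bases its secondary cost-effectiveness analyses on the goal-setting interview and HADS, once as "Interview and HADs outcome measures" and again as "Bangor Goal Setting interview, HADs". The trial outcome list in Protocol 5.2.2.3 has "Generalised Anxiety Disorder Assessment (GAD-7") for anxiety and PHQ-8 for depression, and no HADS.

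**The concern.** Protocol 5.2.2 plans ten one-hour sessions over about three months. An evaluation that closes at month 3 after randomisation closes roughly as treatment ends. It counts most or all of the delivery cost but only the period in which any utility gain is building up, with almost no observation afterwards. Protocol 4.3.3 cites rehabilitation gains that were maintained over time in another condition; a 3-month horizon cannot show whether that happens here.

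Cost per QALY against £20,000 to £30,000 is a stated Workstream 2 research question (Protocol 3.2), so the choice of horizon could decide the answer. The sensitivity analyses described in Protocol 5.2.2.4 give unit costs, staff time, intervention cost and effects as examples. None varies the horizon.

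The HADS point is smaller and separate: an ICER needs an effect measure, and this one would have no data.

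**Working it through.** **No figure to reproduce.** The documents state no utility difference, incremental cost or ICER. What can be derived is how the two horizons compare under stated assumptions.

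**Inputs from the documents.** Economic evaluation at 3 months (Protocol 5.2.2.4). Outcomes at 0, 3 and 6 months from randomisation (SAP 5.2). Treatment over about 3 months (Protocol 5.2.2). Threshold £20,000 to £30,000 per QALY (Protocol 3.2 and 5.2.2.4).

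**Assumptions.** Equal mean utility at baseline and linear change between visits. The between-arm utility gain is d (positive) at 3 months and f × d at 6 months. Incremental costs to 3 and 6 months are C3 and C6, both positive.

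**QALY gain, by area under the curve, time in years.**

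- To 3 months: 0.25 × (0 + d)/2 = 0.125d.
- To 6 months: 0.125d + 0.25 × (d + fd)/2 = 0.125d × (2 + f).

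**Ratio of ICERs.** ICER(3m)/ICER(6m) = [C3/(0.125d)] ÷ [C6/(0.125d(2 + f))] = (2 + f)/(C6/C3).

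| f (share of gain left at 6 months) | 6-month QALY gain | 3-month gain as share of 6-month gain | ICER ratio if C6 = C3 |
|---|---|---|---|
| 1 (all kept) | 0.375d | 33% | 3.0 |
| 0.5 | 0.3125d | 40% | 2.5 |
| 0 (all lost) | 0.250d | 50% | 2.0 |
| -1 (full reversal) | 0.125d | 100% | 1.0 |
| -1.5 | 0.0625d | 200% | 0.5 |

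**Effect of later costs.** The two ICERs are equal when C6/C3 = 2 + f. With f = 1 the ratio is 3/2 = 1.5 at C6/C3 = 2, 3/3 = 1.0 at 3 and 3/4 = 0.75 at 4. With f = 0 it is already 2/2 = 1.0 at C6/C3 = 2. If later service use offsets half the early cost (C6/C3 = 0.5), the ratio rises to 3/0.5 = 6.0 with f = 1 and 2/0.5 = 4.0 with f = 0.

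**Against the threshold (assumed values, C6 = C3).**

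- Extra cost at which £20,000 per QALY is just met, d = 0.05: 0.125 × 0.05 × 20,000 = £125 at 3 months; 0.250 × 0.05 × 20,000 = £250 (f = 0) to 0.375 × 0.05 × 20,000 = £375 (f = 1) at 6 months. These scale with d: for d = 0.03, £75 against £150 to £225; for d = 0.10, £250 against £500 to £750.
- Extra cost £500, d = 0.10: 500/0.0125 = £40,000 per QALY at 3 months; 500/0.025 = £20,000 (f = 0) to 500/0.0375 = £13,333 (f = 1) at 6 months. The conclusion changes.
- Extra cost £1,000, d = 0.05: 1,000/0.00625 = £160,000 at 3 months; 1,000/0.0125 = £80,000 to 1,000/0.01875 = £53,333 at 6 months. The ratio is the same, but the conclusion is not altered.

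**HADS.** The protocol does not expand the abbreviation. No measure of that name is in the Workstream 1 questionnaires (Protocol 5.2.1), the Workstream 2 outcomes (Protocol 5.2.2.3), the SAP 5.2 list, SAP Appendix 1 or the scoring rules in SAP Appendix 2. GAD-7 and PHQ-8 are in all five.

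**The case against.** Five arguments can be made for the plan.

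- **Direction.** A reader might infer that the ICER is bound to be overstated, or that the plan is biased against rehabilitation. The documents do not support that. They contain no utilities, costs or resource-use differences, and the ratio falls below 1 once C6/C3 exceeds 2 + f or the gain reverses far enough. This objection stands, and the 2- to 3-fold figure is conditional. A reversal through cost alone does need 6-month incremental cost above two to three times the 3-month cost for f between 0 and 1, which is less natural when treatment is planned for the first three months. It cannot be ruled out.
- **Timing of cost and benefit.** Sessions are only approximately weekly, and SAP 6.9 anticipates sessions outside their window, so some cost may fall after month 3. Participants apply strategies between sessions, so benefit may start early. This stands: hence most or all of the cost, and linear build-up is an assumption.
- **Unused data.** A reader might infer that the 6-month data will be thrown away. Nothing says so. Service use is recorded over the follow-up period, and further cost-effectiveness and sensitivity analyses are promised. But none of them is stated to run to 6 months.
- **Ambiguity.** The 3-month period could mean the three months after treatment, ending at month 6. Protocol 5.2.2.3 and SAP 5.2 count both visits from randomisation, so month 3 is the more natural reading. If month 6 was meant, the wording still needs correcting.
- **A separate plan.** Health economics lies outside the SAP, so details may sit in another document. CSRI at 6 months rests only on the general sentence in SAP 5.2. Both are fair, and the second calls for confirmation.

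Three months also matches the primary endpoint, which is a reason to keep it as a reported analysis.

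**Conclusion.** The concern holds in a conditional form. What rests on the documents alone is that the economic evaluation is set at 3 months, the schedule that lists EQ-5D-5L and CSRI runs to 6, and no 6-month economic analysis is stated.

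The size rests on four assumptions: equal baseline utility, linear change between visits, f between 0 and 1, and little incremental cost after month 3. Confidence in the arithmetic is high; confidence in the direction is moderate. Because the direction depends on what happens after month 3, the 6-month data are needed to settle it.

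On HADS, a reader might infer that the secondary cost-effectiveness analysis as a whole fails. It does not. Only the HADS-based ICER cannot be run as written; the EQ-5D-5L cost-utility analysis and the ICER based on the goal-setting interview can.

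**What to change.** In Protocol 5.2.2.4, or in a health economics analysis plan if one exists:

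- State the horizon as 6 months post-randomisation. Derive QALYs from the area under the baseline, 3- and 6-month EQ-5D-5L curve, adjusted for baseline utility, and take costs over the same 6 months.
- Report the 3-month result as a sensitivity analysis, which keeps the link to the primary endpoint.
- Confirm that CSRI is collected at 6 months and that its recall periods together cover the whole window. Fill in the EQ-5D-5L and CSRI timepoints in SAP Appendix 1.
- In both places that name HADS, substitute the collected GAD-7 and PHQ-8, or delete it.

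This is a change of wording that uses data already scheduled. The cost is somewhat more missing data at 6 months than at 3, so the missing-data method for costs and QALYs, which the protocol leaves open, should be stated for the 6-month analysis.

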#### Intervention Development.

We will develop phenotype-specific neuropsychological rehabilitation plans targeting the predominantly affected cognitive domains as uncovered in Workstream 1, with methods informed by past work on use of neuropsychological rehabilitation to alleviate cognitive deficits arising from CNS infection. To allow for anticipated heterogeneity in the severity and range of cognitive impairment in people with long Covid, different types of cognitive intervention will be employed, including remediation techniques (e.g. improving attention by lengthening the time to complete simple tasks), compensatory and adaptive strategies (e.g. use of memory notebooks and mnemonics). Our neuropsychological rehabilitation plans for Covid-19 will follow the 2013 NICE guidelines on Stroke rehabilitation (section 1.4. Cognitive functioning), 2013 SIGN guidelines on Brain Injury Rehabilitation and evidence

provided by recent systematic reviews SIGN advises on the approach to address the rehabilitation of memory, attention and executive function and recommends the use of therapies such as meta-cognitive strategies (e.g. problem-solving, goal-management and strategic reasoning to treat executive dysfunction, task-specific training for attentional deficits and the use of external aids (e.g. digital diaries) and internal strategies (e.g. use of visual imagery) for mild-moderate memory problems. Likewise, the NICE guidelines recommend that attention training is focused on relevant functional tasks and training on the use of internal strategies to encode information to treat memory problems, as well as environmental strategies (e.g. environmental prompts) and use of external aids. The goal of the intervention trialled in WS2 is to reduce disability due to 'cognitive Covid' and restore a level of function as similar as possible to level pre-infection.

The interventions will be delivered in 10 individual sessions of 1 hour duration over a period of 3 months (1 session per week approximately). In the first session relevant goals will be identified, alongside with a suite of strategies adjusted to the individual needs based on: 1) existing strategies already tried by the individual and found successful, 2) information from WS1 about the individual's profile of cognitive impairment (e.g. dominant dysexecutive function vs dominant amnesic impairment) and 3) personal preferences.

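### The NICE per-QALY ceiling is applied to acceptability curves for all economic analyses, including BGSI and HADs curves measured in scale points

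*Combined protocol and SAP*

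**What the plan says.** Under Health economic data analysis (protocol 5.2.2.4) a list of components begins with the primary analysis: "Conduct a primary cost-utility analysis using the EQ-5D-5L as the measure of utility". The second component is a secondary cost-effectiveness analysis on trial outcomes ("Bangor Goal Setting interview, HADs), and develop incremental cost-effectiveness" ratios). The third covers both: "For all analyses, we will use bootstrapping to produce cost-effectiveness" acceptability curves, "for comparison with the NICE ceiling of £20,000 to £30,000 per" QALY, so that policymakers can be told how probable it is that the intervention is cost-effective.

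Under Health economic outcome measures, the secondary ratios are defined as incremental cost-"effectiveness ratios (ICERs) to express cost-effectiveness in natural units of effect, which will" "in turn allow comparison with the QALY outcomes. Comparing these outcomes will help to" establish how far the generic and clinical outcomes agree.

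The same section has a fallback. In the "event that neither intervention is found to have a significant effect on patient outcomes, we" (the investigators) regard a robust cost-effectiveness analysis as impossible and will present costs and effects separately as a cost-consequence analysis. The SAP (footnote to its aims) leaves health economics to a separate group, so it does not clarify the threshold.

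**The concern.** The £20,000 to £30,000 figure is a price for one QALY. On a BGSI curve the horizontal axis is willingness to pay per point of a 10-point goal rating. Reading that curve at £20,000 values one point as highly as a full QALY. At such a price, any plausible cost of ten one-hour sessions is small beside the uncertainty in the effect multiplied by £20,000. The curve then mostly answers whether BGSI improved at all, while being labelled as evidence on value for money.

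BGSI is participant-reported and participants know their allocation (protocol 7.3). A clear BGSI difference with little change in EQ-5D-5L is therefore a realistic outcome. Policymakers could then receive a BGSI curve near certainty next to an unfavourable cost per QALY from the same participants. The same unit error applies to HADs.

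**Working it through.** **1. Precision, from the plan's own sample size.** Protocol 7.1 (Power calculation) gives a 2-point important difference, effect size 0.7, 90% power and 5% two-sided significance. The implied SD is 2/0.7 = 2.86, and the baseline SD cited from the earlier trial is 1.74.
- Normal approximation: n per arm = 2(1.960 + 1.282)²/0.7² = 42.9, so 43.
- The t-test version gives 43.87, so 44 per arm and 88 in total, as stated.
- With 25% attrition: 88/0.75 = 117.3, so 118 (59:59), as stated.

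Standard error of the BGSI difference = SD × √(2/44): 0.371 for SD 1.74 and 0.610 for SD 2.86. With t(86) = 1.988, a just-significant unadjusted difference is 1.988 × 0.371 = 0.74 points or 1.988 × 0.610 = 1.21 points.

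**2. Assumptions not in the documents.** The volume is stated ("The interventions will be delivered in 10 individual sessions of 1 hour duration") but no unit cost is. I take an incremental cost of £500 to £3,000 per person, a cost SD of £1,500 or £2,000, and no correlation between cost and effect. The standard error of the cost difference is then £320 or £426. Against 20,000 × 0.371 = £7,419 this hardly matters: both cost SDs give the same probabilities to three decimals.

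**3. Break-even effect if the ceiling is read per BGSI point.** Break-even = incremental cost / λ, where λ is the willingness to pay.

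| Incremental cost | λ = £20,000 | λ = £30,000 |
|---|---|---|
| £500 | 0.025 points | 0.017 |
| £1,000 | 0.050 | 0.033 |
| £3,000 | 0.150 | 0.100 |

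Across these rows, break-even is about 0.8% to 7.5% of the 2-point important difference.

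**4. Height of the curve.** The normal approximation to the bootstrap is P = Φ[(λ·ΔE − ΔC) / √((λ·SE_E)² + SE_C²)]. At λ = £20,000:

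| SD | BGSI difference | £500 | £1,500 | £3,000 | P(effect > 0) |
|---|---|---|---|---|---|
| 1.74 | 0.1 | 0.580 | 0.527 | 0.446 | 0.606 |
| 1.74 | 0.74 (just significant) | 0.972 | 0.963 | 0.943 | 0.977 |
| 2.86 | 0.1 | 0.549 | 0.516 | 0.467 | 0.565 |
| 2.86 | 1.0 | 0.945 | 0.935 | 0.918 | 0.949 |
| 2.86 | 1.21 (just significant) | 0.974 | 0.969 | 0.959 | 0.977 |

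Once the difference is just significant, a sixfold change in cost moves the curve by at most 0.03. At λ = £30,000 the just-significant rows run from 0.957 to 0.975.

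**5. The QALY scale for contrast.** At £1,000 and £20,000 per QALY, break-even is 1,000/20,000 = 0.05 QALY. Over the 3-month evaluation period that is a constant utility gain of 0.05/0.25 = 0.20. At £30,000 it is 0.033/0.25 = 0.13. The same ceiling is therefore a demanding test on QALYs and almost no test on BGSI points.

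**The case against.** A reader might infer that the secondary analysis will call the therapy cost-effective for almost any non-zero effect. The documents do not support that. They set no probability cut-off or decision rule; they plan a curve and a reported probability. At a 0.1-point difference and £20,000 the curve reads only about 0.52 to 0.58 for costs of £500 to £1,500, and below 0.5 at £3,000. A negative estimate would mostly read below 0.5.

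The cost-consequence fallback also helps. At a true effect of 0.2 points BGSI would be non-significant in about 92% to 94% of trials, and at 0.5 points in about 73% to 87%. It is not full protection. Its trigger is patient outcomes in general rather than BGSI, and it lapses once an outcome is significant, which on BGSI can happen well below 2 points.

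The strongest defence is that this is loose drafting. The research questions (protocol 3.2 and 5.2.2.4, SAP 3.2) attach the NICE threshold only to cost per QALY, QALYs are the primary economic outcome, and the secondary analyses are described as comparative. That probably shows the intent, and it protects the primary conclusion. It does not change an instruction that explicitly covers all analyses, with no other text limiting it.

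Nor does the plan say that ratios per point and per QALY will be equated in size. It speaks of agreement between outcomes, and agreement in direction is a fair reading. What it lacks is a statement of which kind of agreement is meant.

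**Conclusion.** The point stands as an error of units in the secondary economic analyses. Followed as written, the plan reads BGSI and HADs curves against a price that does not apply to them, and on BGSI the resulting probability is nearly the probability of any benefit. The mismatch needs no cost figure. Its size does: the values of 0.94 to 0.97 at 0.74 to 1.21 points rest on assumed costs of £500 to £3,000, 44 per arm, unadjusted SDs of 1.74 to 2.86 and uncorrelated costs and effects. Covariate adjustment would probably lower the just-significant difference.

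The claim goes no further. The primary cost-utility conclusion uses the ceiling in its proper units, the clinical primary outcome is untouched, and very small effects give curves near one half rather than a finding of cost-effectiveness. It is worth correcting because policymakers are the stated audience for these probabilities.

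**What to change.** In protocol 5.2.2.4, or in the separate health economics analysis plan:

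- **Threshold.** State that only the cost-utility (QALY) curves are compared with the NICE range, in line with the research questions.
- **BGSI and HADs.** Report incremental cost per point and a curve over a range of willingness to pay per point, with no NICE reference line and no cost-effectiveness statement drawn from that threshold.
- **HADs.** Confirm which measure is meant. HADs is in neither outcome list (protocol 5.2.2.3, SAP 5.2); both list GAD-7 and PHQ-8. Apply the same rule to whichever measure is collected.
- **Agreement.** Under Health economic outcome measures, state that agreement with the QALY result means direction of effect, not size of the ratio.

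This changes a few sentences and needs no new data. The cost is that the secondary analyses no longer yield a single headline probability.
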